#### Attrition, nonadherence and missing data

All analyses will be performed as an intention-to-treat (ITT) analysis to ensure that the clinical efficacy of the treatment is not overestimated as an artifact of attrition (i.e., including all parents/children who completed the baseline). Missing data will be reported, and when MCAR (missing completely at random) or MAR (missing at random) occurs, multiple imputation methods will be used to estimate missing values when appropriate.

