## Methods

### Trial design

This study is designed as an equivalence randomized controlled parallel-group two-arm trial (allocation ratio 1:1) to compare a new blended group intervention (Emotional Detectives In–Out) with a face-to-face group intervention (Coping Cat) for children with anxiety disorders. The Coping Cat intervention was chosen as the active control group because it is an evidence-based cognitive-behavioral intervention for children with anxiety disorders [40, 42] that can be used to test the equivalence of the Emotion Detectives In–Out intervention in reducing anxiety symptomatology. An equivalence trial aims to demonstrate that a novel or non-established treatment is as effective as a well-established treatment within a prespecified margin of equivalence. In the current trial, the margin of equivalence was defined as the difference between the intervention groups that would be considered the minimum clinically relevant difference.

The clinical trial is registered at ClinicalTrials.gov (identifier: NCT05747131, date assigned February 28, 2023). Authorization for sample recruitment was obtained from the Ethics Committee of the Faculty of Psychology and Education Sciences of the University of Coimbra and from the Ethics Committee of the Faculty of Psychology of the University of Lisbon. The clinical trial will follow the ethical recommendations of the American Psychological Association (APA, 2010) and the World Medical Association’s Declaration of Helsinki (World Medical Association, 2013).

The SPIRIT (Standard Protocol Items: Recommendations for Intervention Trials) checklist of information [43] and the CONSORT recommendations for noninferiority and equivalence trials [41] will be used as guidance to report the study protocol of this clinical trial.

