#### Sample size

A minimum sample size of 138 children (69 per group) is needed to test the equivalence between two interventions that do not differ by more than the minimum expected effect size of *d* = 0.50, which is slightly larger than the recommended minimum practical effect size indicated by Ferguson [47]. This calculation is based on the two one-sided tests (TOST) procedure for determining equivalence as outlined by Lakens [48] and using the authors´ TOSTER package for R, assuming equal group allocation, alpha = 0.05, 80% power, and four measurements. This sample size is also sufficient to detect within-subject changes in anxiety scores of the same magnitude (*d* = 0.50) over four measurements (WebPower; [49]). With this sample and allowing for a substantial violation of sphericity, the achieved power is 97%. Finally, an *N* = 138 with four measurements is sufficient for growth mixture modeling [50]. With an attrition rate of 15% [19, 51], we will have to recruit approximately 165 parents at T0 to achieve the final intended sample size.

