##### Feasibility of the intervention

The feasibility of the programs will be measured through adherence (number of sessions attended and number of treatment completers, defined as those who participated in at least 70% of the sessions) and dropout rates (number of participants who dropped out from the intervention before completing it). In the Emotion Detectives In–Out condition, the pattern of online session usage by both children and parents will be assessed based on the number of completed online sessions, the timing of the completed online sessions (within the designated week or not), the number of pages accessed in each session, the number of website logins, the number of interactive exercises completed in each session, and the completion of home assignment tasks within the program platform.

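### ITT is fixed for every analysis with a rationale that does not guard against false equivalence, and no equivalence test in adherent children is planned alongside it

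*Protocol article*

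**What the plan says.** The Trial design section describes an equivalence trial: "This study is designed as an equivalence randomized controlled parallel-group two-arm trial (allocation ratio 1:1"). The Efficacy evaluation section makes the primary equivalence test a between-group TOST at postintervention and at 3 months. Under Sample size, the effect size used as the margin is d = 0.50, and 138 children (69 per group) is the number that "is needed to test the equivalence between two interventions that do not differ by more than the minimum expected effect size of" that value.

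The section headed Attrition, nonadherence and missing data fixes the analysis set: "All analyses will be performed as an intention-to-treat (ITT) analysis to ensure that the clinical efficacy of the treatment is not overestimated". The sentence goes on to name attrition as the source of that overestimation, and defines the set as all families who completed the baseline. Missing values under MCAR or MAR are to be handled by multiple imputation where appropriate.

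Adherence is defined elsewhere. The Feasibility section counts the "number of treatment completers, defined as those who participated in at least 70% of the sessions", but only as a feasibility outcome. The only loss rate given is under Sample size: "With an attrition rate of 15% [19, 51], we will have to recruit approximately 165 parents at T0".

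**The concern.** The stated reason for ITT is that it avoids overestimating efficacy. That is the relevant protection when the claim is that one arm is better. Here the claim is that the arms differ by no more than 0.50 SD, so the costly error is a missed difference. A child who is assigned to a programme but takes little of it contributes little to the contrast between programmes. If this happens in both arms, the ITT difference moves towards zero, which is the direction that supports the claim.

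Because the rule covers all analyses, the primary TOST included, it is a choice the article makes and not a detail left for later. A later plan that added a per-protocol TOST would contradict it. At stake is whether a finding of equivalence can be read as the two treatments working equally well, or partly reflects incomplete uptake of both.

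**Working it through.** **Inputs from the protocol article.** Margin d = 0.50 in SD units (so SD = 1), 69 per arm, about 165 recruited, 15% attrition (Sample size). The test settings there are "assuming equal group allocation, alpha = 0.05, 80% power, and four measurements". A true difference of zero for the power calculation is an assumption, since none is stated.

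**Inputs not in the article.** No non-adherence rate is given for either arm. The 15% attrition rate is used below only as a reference point, within an assumed range of 5% to 30%.

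**Step 1: reproduce the plan's figure.** For TOST with zero true difference, n per arm = 2 × (z₀.₉₅ + z₀.₉₀)² / d² = 2 × (1.645 + 1.282)² / 0.25 = 68.5, rounded up to 69. This matches. Power at 69 per arm is 80.4% by the normal formula and 80.0% by t-based simulation. Recruitment: 138 / 0.85 = 162.4, so 163, consistent with about 165.

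**Step 2: acceptance region.** With 69 per arm, SE = √(2/69) = 0.1703. TOST declares equivalence when the observed difference lies within ±(0.50 − 1.645 × 0.1703) = ±0.220. If the true difference is exactly 0.50, this happens with probability Φ((0.220 − 0.50)/0.1703) = 5.0%, as it should. The lower bound contributes a negligible amount here and below.

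**Step 3: equal dilution in both arms.** Let the difference among adherent children be 0.50, and let a fraction f in each arm be non-adherent with no between-arm difference. The ITT difference is 0.50 × (1 − f), and the probability of declaring equivalence is Φ((0.220 − ITT difference)/0.1703).

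| f (assumed) | ITT difference | Declared equivalent, 69 per arm | 82 per arm |
|---|---|---|---|
| 0% | 0.500 | 5.0% | 5.0% |
| 5% | 0.475 | 6.7% | 6.9% |
| 10% | 0.450 | 8.8% | 9.3% |
| 15% | 0.425 | 11.4% | 12.2% |
| 20% | 0.400 | 14.5% | 15.8% |
| 30% | 0.350 | 22.2% | 24.7% |

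**Step 4: partial dilution.** If the 15% who are non-adherent keep half the difference, the ITT difference is 0.85 × 0.50 + 0.15 × 0.25 = 0.4625, and the probability is 7.7%.

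**Step 5: unequal non-adherence.** Assume benefits of 1.0 SD for Coping Cat and 0.5 SD for the new programme, and none for non-adherers.
- 15% non-adherent in Coping Cat, 5% in the new programme: 1.0 × 0.85 − 0.5 × 0.95 = 0.375, giving 18.1%.
- 5% in Coping Cat, 15% in the new programme (the less effective arm in this illustration): 1.0 × 0.95 − 0.5 × 0.85 = 0.525, giving 3.7%. Here ITT is conservative.

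**Step 6: what a second analysis costs.** With 70 children per arm analysed, zero true difference and no selection, the simulated probability that both the ITT and the per-protocol TOST succeed is about 75% with 66 per arm in the per-protocol set and about 67% with 58 per arm. ITT alone succeeds about 80% of the time.

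**The case against.** Several points against the concern stand, and they limit it.

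- **The estimand.** If the effect of assignment is 0.425, it lies inside the margin, and an ITT TOST that declares equivalence is right about that question, with its 5% error intact. The excess is an error only for the effect among adherent children. The effect of assignment is a legitimate target here, because better compliance and lower dropout are among the expected advantages of the blended format (introduction and Discussion).
- **Attrition.** A reader might infer that attrition and imputed values pull the arms together by themselves. The article does not support that. Multiple imputation within arm under MAR need not shrink the difference, and nothing in the article says that arm is ignored. The clearer route is non-adherence.
- **Direction.** A reader might also infer that ITT is always anti-conservative in this trial. Step 5 shows a case where it is not, and the article gives no adherence rates by arm.
- **Size.** A child who attends 60% of sessions counts as a non-completer but has received most of an active programme, so a zero between-arm difference among non-completers is an extreme assumption.
- **The rationale.** Guarding against artefacts of attrition is a valid aim in an equivalence trial too. If one arm loses more poor responders, an analysis of completers flatters it. The reason given is incomplete, not wrong.
- **Adherence is not ignored.** Moderation by homework frequency and by involvement in therapy is planned.

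What remains is that none of this gives an equivalence test in children who took the treatment. The moderation analyses do not test the contrast against the margin, and the ITT rule as worded leaves no room for one that does.

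**Conclusion.** The concern holds as a risk that depends on non-adherence. The article fixes ITT for the primary TOST on a rationale that does not address a false conclusion of no relevant difference, and it uses its completer definition only for feasibility. If the difference among adherent children sits at 0.50 and 15% in both arms are non-adherent with no between-arm difference, ITT declares equivalence 11.4% of the time at 69 per arm instead of 5%. It is 7.7% if non-adherers keep half the difference, and 3.7% in the example where non-adherence is concentrated in the less effective arm. Across assumed equal dilution of 5% to 30% the range is 6.7% to 22.2%. These are sensitivity figures, not estimates, and they count as error only for the effect among adherent children.

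The sample size of 138 reproduces and is not in question. ITT should stay.

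**What to change.** Under Attrition, nonadherence and missing data:

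1. Keep ITT, and state that it estimates the effect of being assigned to each programme. State that imputation is done within arm.
2. Pre-specify the same TOST, at postintervention and at 3 months, in a per-protocol set defined by the attendance threshold already in the Feasibility section (at least 70% of sessions).
3. Report both 90% confidence intervals against ±0.50. Treat equivalence as robust only if the two analyses agree, and discuss any disagreement as a limit on the claim.
4. Replace the rationale with one suited to equivalence: ITT guards against bias from selective loss, and the per-protocol analysis checks that equivalence is not produced by non-adherence.

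No new data are needed, since session attendance is already recorded, and the target N does not change. There are three costs. The per-protocol set will be smaller by an amount the article does not allow one to state: the 15% is attrition, not the share attending under 70% of sessions, so one cannot assume that 165 × 0.85 ≈ 140 children would qualify. That set is also open to selection bias, possibly different by arm because the session schedules differ, so it complements ITT and does not replace it. Finally, asking for agreement lowers the chance of a robust claim to about 67% to 75%, with 58 to 66 per-protocol children out of 70 per arm and no true difference. For that reason a strict rule that both must pass is a trade-off for the investigators to decide, and it should be settled before the data are seen.

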### Data monitoring

No data monitoring committee, interim analyses, or auditing will be implemented for the study. The research team will engage in ongoing discussions about important ethical issues, particularly those associated with adverse events or unintended effects, throughout the trial. For example, in cases where a serious psychological problem (such as psychotic symptoms or suicidal ideation) is identified during the eligibility interview and cannot be addressed within the current study, immediate communication will be established with the parents/legal representatives of the children. In such instances, the child will be promptly referred to a pediatric mental health service. Furthermore, if a child experiences a worsening of symptoms between the enrollment phase and the start of the intervention, their parents/legal representatives will be promptly notified. The research team will conduct a thorough assessment, and the need for referral to another type of intervention will be considered.

### Ethics and dissemination

Authorization for sample recruitment was obtained from the Ethics Committee of the Faculty of Psychology and Education Sciences of the University of Coimbra and from the Ethics Committee of the Faculty of Psychology of the University of Lisbon. Parents/legal representatives of eligible children will be requested to provide written informed consent, while the children themselves will be asked to provide their assent. All parents/legal representatives will receive information about the voluntary nature of their participation and that of their children. Those recruited at the child mental health services of the collaborating hospitals will be informed that declining to participate in the study will not impact the medical/psychological care available to their children. Additionally, parents/legal representatives will be informed that they have the right to drop out from the study at any time and for any reason (or without specifying a reason), without influencing the care provided. In cases where children or parents express a preference for individual psychotherapy rather than on the offered group interventions, they will be directed to a child psychologist for individual CBT, and their case will be excluded from the trial. All parents/legal representatives will be informed that all data collected will be utilized only at an aggregate level (e.g., average scores of all participants in the questionnaires) and that participants' identities will not be revealed in any reports or publications resulting from the study. After study completion, potential identifiers, such as study ID, will be deleted from the database (database anonymization).

The results of the study will be disseminated to both the scientific and general communities through various means. Dissemination outputs will include fact sheets, research conference posters and oral presentations, as well as scientific articles submitted to international peer-reviewed journals. The authors of these outputs will be members of the research team who have made significant and direct contributions to the study design, data collection and analysis, and manuscript writing. The research team also aims to disseminate the study findings to professionals in the field of child mental health, such as pediatricians, child psychologists or psychiatrists, school teachers, and psychologists. This dissemination will be achieved through lectures, information sessions, and/or the distribution of informative brochures at healthcare centers, hospitals, or schools.

## Discussion

The goal of this clinical trial is to compare the efficacy of a new delivery format of an effective psychological intervention for children’s EDs (the UP-C; [87]) in comparison with an established EBT (the Coping Cat). We anticipate that the Emotion Detectives In–Out will be a viable and cost-effective alternative intervention for treating children's EDs that allows for a large increase in children's access to care (e.g., fewer clinic visits, lower costs). We also expect it to increase children’s adherence, decrease dropout, and improve transfer to everyday life (e.g., online sessions support behavior change during face-to-face sessions and will be available when convenient), which will contribute to the intervention's efficacy. This new intervention may also result in significant cost savings for health institutions (due to fewer clinical consultations) and more time available for therapists, which in turn may contribute to the reduction of waiting lists and the timely attendance of children in need. In addition, by targeting common transdiagnostic mechanisms across several disorders, the Emotion Detectives In–Out intervention may eliminate the burden of training for several single-disorder protocols as therapists only need to learn this intervention to provide evidence-based care for the most common childhood EDs.

## Data Availability

No datasets were generated or analysed during the current study.
